**Fig. 2 Fig2:**
[figure not shown]
Protocol flowchart

**Table 2 Tab2:**
[figure not shown]
Schedule of enrolment, interventions, and assessments

*Digit span, Arithmetic span, symbol span, spatial addition, DalCAB

** Digit span, Arithmetic span, symbol span, spatial addition, DalCAB, training gains

##### Baseline session

After the informed consent process is carried out, eligible participants are administered the baseline measures (T0). The baseline data are included in data analyses as potential modifiers of performance. The baseline measures involve completing a series of questionnaires (Table 5). On the same day of baseline testing, patients are given a diary for them to keep. The diary contains information on how to setup and use the training program on their computer, education on how to do the working memory training, general troubleshooting information, and also a daily table to record information about the training session and any issue they might experience. The diary also contains contact details of the researcher administering the stimulation and information about future appointments. In addition, participants are asked to refrain from excessive alcohol or caffeine intake during the testing and to maintain good sleeping habits, where possible. In total, we expect the entirety of the first in-lab session (informed consent, screening, and baseline measures (T0)) to take about 1 h.

##### Outcome assessment (T1)

On the following day participants perform a series of pre-training outcome tasks (T1; Table 4), administered by an assessor, to measure their baseline working memory capacity and to assess, during and at the end of the training intervention, the efficacy of the training and the stimulation regime. These tests will not be used to determine eligibility. The assessor is blind to group assignment (control vs active).

On the same day as T1 testing, the assessor will familiarize them with the stimulation procedure (which is identical for sham or active) and the training game. The member of the team administering the training answers any questions about the study. Overall, this second session lasts for about 1 h.

##### Training phase 1

On the 10 consecutive training days after the T1 session, depending on the group, participants will receive active or sham brain stimulation (see section 3.5.2). As the assessor, who administer brain stimulation, is blind to the intervention, the procedure will be the same for both groups. At the same time, both groups complete the working memory training exercise for 20 min. If the WM training finishes before the stimulation, participants are asked to wait until the end of the tDCS session (20 min). Before each training session, participants are also asked to answer short questions (level of alertness, engagement, etc.). Once the training session and the stimulation are complete, the participant fills in a feedback form on the side effects of brain stimulation experienced, if any.

Participants will complete 10 consecutive training sessions (2 weeks, excluding weekends. Each session should take about 45 min (~ 10 min setting up of tDCS and ~ 20 min of WM training). This phase will be completed at home, with the assistance of the trainer. An attempt will be made to start the intervention on a Monday, therefore aiming to have breaks in the stimulation at the same point in the 2 weeks, and to keep the training time consistent over days. Nevertheless, administration time and date will be recorded. By the end of these 10 sessions, participants will be familiar with the training game and will be able to confidently undertake the training by themselves in the next 15 sessions.

##### Outcome assessment (T2)

When the first 10 days of training are complete, the participant will undergo time 2 (T2) assessment. As before, testing involves completing a series of computerised cognitive tasks to measure training gains and transfer (see 3.5.6). This assessment will also include the tests from the WAIS-IV and WMS-IV (Table 3).

**Table 3 Tab3:** Screening tasks

Task	Description
Digit Span (WAIS-IV)	The patient is read a sequence of digits, to repeat forwards, backwards or in ascending order of magnitude (sequence).
Arithmetic (WAIS-IV)	The patient is read a number of mathematical problems increasing from very simple to complex in terms of the amount of information the person has to hold in mind.
Symbol Span (WMS-IV)	Patients are asked to look at a series of symbols for 5 s then choose which symbols they saw from a multiple-choice format, pointing to them in the order they were shown from left to right. The test progresses from only one symbol with the sequence increasing depending on how well people do.
Spatial Addition (WMS-IV)	The patient is shown a grid for 5 s, then a second grid for 5 s. The grids contain blue and red circles. The patient is provided with a number of cards showing red, blue or white circles and asked to place them onto a cardboard grid according to the following rules: Place a blue circle in any place where you saw a blue circle on only one of the pages. Place a white circle in any place where you saw a blue circle in the same place on both pages. Ignore red circles.

##### Training phase 2

Participants will then start the second training phase, involving 3 weeks of working memory training only (no brain stimulation). During this phase, patients will access the training program via internet at home on their own. Manualised weekly phone calls using a semi-structured script will be used to monitor the patients progress and to address any issue they might experience.

##### Outcome assessment (T3)

When the second 3-week training phase is complete, participants will undergo time 3 (T3) assessment, during which they repeat the same series of computerised cognitive tasks as in T2 (Table 4).

**Table 4 Tab4:** List of outcome measures

TASK	DESCRIPTION	Target functions
Simple Reaction Time	Respond to each stimulus, with varying response-stimulus intervals.	Vigilance
Go/No-Go	It employs a continuous stream of two different stimuli for which a binary decision must be made, such that one stimulus type requires a response (go) and the other stimulus type requires the participant to withhold a response (no-go).	Executive control
2-Choice Reaction Time	Indicate the colour of each stimulus (2-choice responses; 50% each choice).	Vigilance
Dual task	Complete the 2-choice reaction time task while silently counting the number of each colour of stimuli presented. Count probe for one colour at the end of each set.	Executive control
Flanker	A central target stimulus is presented with flanking stimuli (flankers) on two sides that are either the same as (congruent) or different than (incongruent) the central target stimulus. The participant must decide and respond regarding a feature of the central stimulus (e.g., red or black) while ignoring/filtering the flanking stimuli.	Executive control
Item Working memory	Indicate whether a probe item was present or absent in a preceding study set of 2–6 items (50% present).	Working memory
Location working memory	Indicate whether a probe item was present or absent in the same position in a preceding study set of 2–6 locations (50% present).	Working memory
Visual search	Locate and indicate orientation (upright vs. inverted; 50% each) of a target among different shape distractors that are a different colour (feature search) or the same colour (conjunction search) as the target.	Orienting and Selection
Fixed visuo-spatial n-back task	Participants must attend to a visual stream of information that is presented sequentially and look for matches, pressing a button upon seeing a “match”. Three levels of difficulty will be used (n = 1,2,3)	Working memory

##### Outcome assessment (T4)

A final follow-up assessment, identical to the one at T2 and T3, will be carried out 1 month after the completion of the intervention, to assess maintenance of working memory improvements and transfer.

#### Cognitive tasks and questionnaires

A series of cognitive tasks will be administered at different time points and for a different purpose during the study: *screening*, *training*, and *outcome assessment*.
Screening: the Digit Span, Arithmetic, Symbol Span, and Spatial Addition subtests from the WAIS-IV and WMS-IV will be used for screening participants for cognitive impairment (see 3.5.4, 35 min to complete). A description of the task is given in Table 3.Training Task: The visuo-spatial training task is a visuo-spatial adaptive n-back (see section 3.5.3).Outcome: 1) the Dalhousie Computerized Attention Battery (DalCAB, [68], 35 min to complete) will be used as the outcome assessment battery. A description of the tasks in the battery is provided in Table 4. For a detailed description of the parameters used in each task see [68]; 2) In addition, a non-adaptive visuo-spatial N-back task will also be used as outcome measure, with fixed levels of *N* = 1,2,3. (~ 30 min to complete); 3) The Digit span, Arithmetic span, Symbol span and spatial addition will also be used as outcome measures.A series of questionnaires and feedback forms will also be administered at single or multiple time points throughout the intervention to record variables that may impact or may be affected by performance on the task. Permission to use these instruments has been obtained for those questionnaires requiring it. A list of the questionnaires, together with a brief explanation and references is presented in Table 5.

**Table 5 Tab5:** Questionnaires

	Questionnaire	Taken at
*Individual lifestyle*	Participant Health History (including details on injury, medications etc..)	T1
	Epworth Sleepiness Scale (to report habitual sleepiness [62]	
	Quality of life assessment (The Whoqol Group [63]), − in four facets (Physical health, Psychological, Social relationships, Environment)	
*Individual cognitive state*	Cognitive Failures Questionnaire (CFQ, [64]) to measure self-reported failures in perception, memory, and motor function.	T1
	Hospital Anxiety and Depression Scale (HADS) to measure emotional symptoms (HADS; [65])	
	Patient Reported Evaluation of Cognitive Status (PRECiS [66];)	T1/T3/T4
*Feedback on the of intervention*	Side effect of the tCS [57]	Every tCS session
	System usability scale (SUS [67];)	T3
	Attitude towards stimulation (to record how they feel their attitude towards the brain stimulation affected performance)	
	Feedback on strategy (to record whether they use a specific strategy to complete the training task)	
	Blinding questionnaire (to confirm efficacy of the blinding procedure)	T4

#### Outcome measures

Our primary outcome measure will be the training gain*,* obtained by looking at the relative change in n-level (# items maintained in working memory) over the course of the training, as well as performance increments in the pre−/post-test outcome measures in the stimulation relative to the control (SHAM) group. Transfer of improvement to other cognitive domains will be assessed by comparing performance in a battery of cognitive tasks given at different times points throughout and after the intervention. Maintenance of improvement will be assessed by comparing outcome measures (Table 4) at different occasions during and after the conclusion of the study.
Training gain. Performance in training is measured as the N level reached on every session. The training gain is defined as the difference in N levels at two time points. Accuracies and reaction times at trial level will also be collected. In addition, we will administer a non-adaptive visuo-spatial task (N = 1, *N* = 2, *N* = 3), to allow us to quantify improvements at different testing points in terms of accuracy and reaction times in the trained cognitive domain.Transfer. We will use spatial tasks that test the same cognitive process as the training task to evaluate transfer to closely related tasks. We will use the same spatial addition and the symbol span task also used in the screening phase. We also will use the Dalhousie Computerized Attention Battery (DalCAB) [68], 8 cognitive tests to assess attentional functions in the vigilance, orienting and executive control attention network. Tasks are described in Table 4. Reaction time and accuracy will be computed for each task.Maintenance. To identify how long benefits of training and or stimulation are maintained in time, we will compare changes between outcome measures at T3 and at T4, 1 month after the end of the intervention.Everyday life improvement. It is important to understand whether improvement in cognitive tasks targeting specific processes can transfer to improvement in everyday life activities. We will use a self-reported questionnaire (PRECIS, Patchick et al., Clinical Rehabilitation, [66]) to evaluate if and how training in cognitive tasks targeting specific processes impacts on everyday activities.

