## Aims and objectives

The aim of this research project is to investigate the impact of combined working memory training and tDCS protocols in individuals following a brain injury in terms of the training gains, change in objective measures of working memory, mood and fatigue, as well as participants’ perceptions of day-to-day memory function and subjective benefit of the training program.

Specifically, our primary objective is to determine if the combination of tDCS and working memory training is superior to working memory training alone to improve working memory function in an n-back task in an ABI population. The key secondary objectives are to determine if the combination of brain stimulation with working memory training can:
boost performance in other cognitive domains (attention, executive functions)speed training gainslengthen improvement duration to 1 monthincrease improvement magnitude

To address the above questions, we will use a randomized clinical trial, assessor- and patient-blinded with two parallel groups and a simple randomization with a 1:1 allocation ratio.

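### The primary outcome sentence joins training gain to the pre/post-test measures, conflicts with the n-back primary objective, leaves gain loosely defined, and has no error control across the measures it names

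*Protocol article*

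**What the plan says.** All references are to the protocol article.

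- **Primary outcome (Outcome measures).** Training gain is described with the words "by looking at the relative change in n-level (# items maintained in working memory) over the course of the training, as well as performance increments". Those increments are on the pre/post-test outcome measures, compared "in the stimulation relative to the control (SHAM) group". No pre/post measure or visit is singled out.
- **Primary objective (Aims and objectives).** The question is whether adding tDCS "is superior to working memory training alone to improve working memory function in an n-back task in an ABI population". Attention and executive functions are listed under key secondary objectives.
- **Definition of gain (Outcome measures, Training gain item).** "Performance in training is measured as the N level reached on every session", and then: "The training gain is defined as the difference in N levels at two time points". The two points are not named. The fixed n-back at levels 1, 2 and 3 appears in the same item.
- **Transfer (Outcome measures, Transfer item).** Spatial addition, symbol span and the eight DalCAB tests are assigned here. For these: "Reaction time and accuracy will be computed for each task".
- **Error control (Data collection, management, analysis, and monitoring).** Main effects and interactions are judged at p < .05. Multiple-comparison correction applies to the post-hoc tests that follow a significant result.
- **Sample size.** The calculation is for one between-group comparison at effect size 0.73, giving about 48. Forty are planned.

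**The concern.** Three statements bear on what is primary, and they disagree. The objective points to an n-back task. The outcome sentence adds the pre/post-test measures. The Transfer item then places most of those measures outside the primary question. Even the objective leaves open whether the adaptive training task or the fixed outcome task is meant.

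Training gain is not pinned down either. A relative change and a difference rank patients alike only if all start at the same level. There are 25 sessions (10 with stimulation, then 15 without), so a gain measured to session 10 answers a different question from a gain measured to session 25. Each session has 20 blocks and restarts at level 1, so the level reached could be the highest, the last or an average.

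At stake is whether the criterion for a positive trial is settled before the data are seen. As written, more than one result could be presented as the primary result, each tested at .05.

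**Working it through.** **1. The plan's own figure.** With d = 0.73, power 0.80 and equal arms, n per arm = 2(z_α + z_β)²/d².
- One-sided .05: 2(1.645 + 0.842)²/0.5329 = 23.2, so 24 per arm and N = 48. This reproduces the stated figure.
- Two-sided .05: 2(1.960 + 0.842)²/0.5329 = 29.5, so 30 per arm and N = 60 (62 with the t distribution).

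The article does not state sidedness. For this point, what matters is that either version is for one test.

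**2. How many measures the primary sentence can cover (one occasion).**
- Narrow reading, training gain plus fixed n-back: 1 + 2 = 3 if n-back level is an ANOVA factor (reaction time and accuracy), or 1 + 3 × 2 = 7 if each level is scored separately.
- Literal reading, by task: gain + 9 tasks in Table 4 = 10. Adding the four Wechsler subtests named as outcomes gives 14.
- Literal reading, by score: 1 gain + 8 × 2 DalCAB + 3 × 2 fixed n-back + 4 subtests = 27.

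**3. Chance of at least one p < .05 when no measure truly differs.** For independent tests this is 1 − 0.95^k. For example, 1 − 0.95^3 = 14%, 1 − 0.95^7 = 30% and 1 − 0.95^27 = 75%. With correlation, I simulated k equally correlated normal test statistics (200,000 draws per setting). The correlations are assumptions, because the article gives none.

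| Measures | ρ = 0 | ρ = .3 | ρ = .5 | ρ = .7 |
|---|---|---|---|---|
| 3 | 14% | 14% | 13% | 11% |
| 7 | 30% | 27% | 23% | 18% |
| 10 | 40% | 35% | 29% | 21% |
| 14 | 51% | 44% | 35% | 25% |
| 27 | 75% | 63% | 48% | 33% |

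**4. Counting only results that favour active.** Here the reference for one two-sided 5% test is 2.5%. Independent tests give 1 − 0.975^k.

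| Measures | ρ = 0 | ρ = .7 |
|---|---|---|
| 3 | 7% | 5% |
| 7 | 16% | 9% |
| 10 | 22% | 11% |
| 14 | 30% | 12% |
| 27 | 50% | 16% |

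**5. Cost of keeping several measures primary.** With d = 0.73, 20 per arm and a two-sided t-test, power for one primary is 61%. With Bonferroni correction it is 50% for 2 measures, 27% for 10 and 17% for 27. The total N for 80% power would be 74, 104 and 124 respectively.

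**The case against.** **The battery was not meant to be primary.** The outcome sentence opens by naming a single measure, training gain. The sentence after it moves to transfer, and the Transfer item covers 18 of the 27 scores (16 DalCAB, 2 Wechsler). Read with the objective, the intended family is training gain plus the fixed n-back. This largely stands, and it is why the 3-to-7 range is given first. It does not remove the conflict: the added clause is in the primary sentence, and even three measures tested at .05 exceed 5%.

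**A false positive primary result is not likely.** A reader might infer that chance alone would probably produce one. The figures do not support that. The probability exceeds one half only at about 14 near-independent tests, or at 27 with weak to moderate correlation. Counting only results that favour active, it reaches at most about 50%.

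**Visits are not free extra tests.** A reader might also multiply the count by the assessments at T2, T3 and T4. The planned repeated-measures ANOVAs would ordinarily test visits together and correct the follow-ups, so no such multiplication is made here.

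**Relative may only mean relative to the start.** Possibly so, since only the second sentence is offered as a definition. Then deleting the word costs nothing. The unnamed time points remain. How much power a relative-change score would lose cannot be derived from the article, because it gives no starting levels or standard deviations.

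**Multiplicity belongs in the analysis plan.** That holds for secondary and transfer outcomes. Which variable is primary is stated in this text, and stated inconsistently.

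**Conclusion.** The point holds in this form: the primary outcome sentence contradicts the primary objective and the Transfer item, gain is described in two ways without time points, and no stated rule controls error across the measures that the primary sentence names. The size depends on the reading. The narrow one gives roughly two to six times the nominal 5%, and the literal one roughly four to fifteen times. These ratios assume that every measure is tested once at .05, that no measure truly differs between groups, and equal correlations between 0 and 0.7. The defect is present at every count examined. It is one of definition and can be cured before analysis.

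**What to change.** 1. In the primary outcome sentence, delete the clause that adds performance increments in the pre/post-test measures.
2. Name one n-back measure as the sole primary outcome, tested at .05. N-level training gain is one example.
3. If training gain is chosen, use the absolute difference (delete the word relative) or the final level adjusted for the starting level. State which.
4. Name the start and end sessions, and say how a session's N level is scored from its blocks. Whether the end point is the end of stimulation or the end of the 5-week training is the investigators' choice, but it must be fixed in advance.
5. Label the fixed n-back as key secondary if it is not primary, and the DalCAB and Wechsler measures as transfer outcomes, secondary or exploratory.
6. Make the primary objective say which n-back task it means.

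The cost is wording in the protocol and any matching registry entry. Fewer measures can be claimed as confirmatory. The single primary test then has a 5% error rate, and the one-comparison sample size calculation refers to the test actually made.

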### Data collection, management, analysis, and monitoring

Accuracies and reaction times at trial level will be collected, alongside the ‘n’ level for each block. Data will continuously be monitored for completeness and consistency. Data entry will be double-checked, and data quality will be ensured based examination of ranges. Prior to statistical analysis, we will test the distribution of the scores. We will analyse the data using appropriate statistical methods, including mixed and repeated measures ANOVAs, with factors of group and test variables. Variables potentially modulating the outcome of the intervention (such as age or time since injury) will considered as regressors in the analysis. Scores that are non-normally distributed will be analysed with non-parametric tests. Significant main effects and interactions (*p* < .05) will be followed by post-hoc tests corrected for multiple comparisons. Dependent variables on the computerized tasks will include mean reaction time (RT) and accuracy (% correct). The research team will analyse the data with a combination of SPSS, JASP, R, Python, and MATLAB.

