**Exclusion criteria**	
1. Pre-injury psychiatric or neurological disease by self-report (e.g., anxiety disorder, ADHD, Parkinson’s disease, etc.) 2. History of diagnosed severe depression (diagnosed pre-injury) 3. History of epilepsy (diagnosed pre-injury) 4. Family history of epilepsy 5. Have had fainting spells or syncope in the last 3 years pre-injury 6. Have significant hearing loss, vision or motor impairment that would prevent them from performing the task 7. Known to be pregnant 8. Consuming medication affecting cortical excitability or recreational drugs^a^ 9. Metal (except titanium) or electronic implants in the brain /skull (e.g., splinters, fragments, clips, cochlear implant, deep brain stimulation, medication pump…) 10. Metal (except titanium) or any electronic device at other sites in your body, such as cardiac pacemaker or traumatic metallic residual fragments 11. Have skin problems such as dermatitis, psoriasis or eczema under the stimulation sites 12. Have had brain stimulation in the past 6 months 13. Have undergone transcranial electric or magnetic stimulation in the past (more than 6 months) which resulted in adverse effects 14. Skull fractures, significant skull defects, skull plates or large vessels occlusions, no significant cortical lesion or atrophy at the site of electrode 15. Having had a seizure at the time of accident or between the injury and starting of the therapy.	

^a^We follow recommendations by McLaren et al. [49], and only exclude drugs that are shown to block tDCS effects (e.g., sodium channel blockers, calcium channel blockers, and NMDA receptor antagonist), while other medications shown to only modulate tDCS effects will be tracked and considered as covariate in the analysis. We will monitor for medication changes as a potential bias on the outcomes of the intervention and report any changes that may occur. If a patient become in need of medications shown to block tDCS effects, they will be excluded from further participation. We will monitor changes in medication and general health through in-person briefing during the first 2 weeks of the intervention, when a researcher is visiting the patient’s house, and via phone calls (e.g. “Have there been any changes in your health or medications since our last phone call?”) during the remaining 3 weeks of the intervention

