## Discussion

The overarching aim of the study is to assess if a specific form of non-invasive brain stimulation, namely direct current, has an impact on performance during a working memory training regimen in patients with an acquired brain injury. The novelty of our research resides in the combination of brain stimulation with working memory training: while the two interventions have been used before in clinical populations, to the best of our knowledge this is the first trial looking at the combination of both in acquired brain injury patients.

The focus of this study are chronic brain injury patients. These patients are no longer in a clinical setting but have returned home and are seen by the Community Brain Injury Service for community-based rehabilitation. These aspects make the proposed intervention particularly suitable for the population under study, as individuals can undertake the long (5 weeks) training regimen in the comfort of their home, at their own pace, minimizing the risk of drop-outs otherwise likely with long interventions. Our intervention is suitable for home healthcare, and, if proven successful, could represent a valuable asset to the NHS to address brain injury related cognitive impairment without putting excessive burden on patients and carers, and the NHS. At the same time, this trial will provide valuable knowledge to health authorities and the research community on the potential of non-invasive brain stimulation and training regimens in addressing chronic cognitive impairment in clinical populations. If successful, our study will provide evidence that a restorative approach to cognitive rehabilitation is possible, and an alternative to compensatory approaches currently used.

By evaluating performance at 1 month after the completion of the training regimen, we will shed new light on the long-term effects of cognitive training, also identifying potential modulatory effects of brain stimulation. This finding will, in turn, inform future protocols, in order to maximise improvement of cognitive functions while minimizing the amount of training necessary. Ultimately, patients would want these interventions to have an impact on their everyday life: we therefore also ask patients to self-evaluate (with the PRECIS questionnaire) how the training regimen impacted their cognitive functions and, indirectly, on their ability to cope with everyday situations.

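### The named longitudinal method, mixed or repeated-measures ANOVA, compares completers at T3 and T4, and at T2 as well if run across all visits; a likelihood-based mixed model would keep the observed T2 scores

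*Protocol article*

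**What the plan says.** The analysis sentence, under 'Data collection, management, analysis, and monitoring', reads: "We will analyse the data using appropriate statistical methods, including mixed and repeated measures ANOVAs, with factors of group and test variables". The same paragraph adds non-parametric tests for non-normal scores and corrected post-hoc tests after significant main effects and interactions. No other longitudinal method is named.

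Outcome tests are given at four visits:
- T1, before training.
- T2, after stimulation: "When the first 10 days of training are complete, the participant will undergo time 2 (T2) assessment".
- T3, after three further weeks of unsupervised training.
- T4, which "will be carried out 1 month after the completion of the intervention, to assess maintenance of working memory improvements and transfer".

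'Outcome measures' also describes two-point comparisons. For training: "The training gain is defined as the difference in N levels at two time points". For maintenance: "we will compare changes between outcome measures at T3 and at T4, 1 month after the end of the intervention".

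Incomplete series are foreseeable. The Discussion presents home training as "minimizing the risk of drop-outs otherwise likely with long interventions", and the footnote to the eligibility table says: "If a patient become in need of medications shown to block tDCS effects, they will be excluded from further participation". 'Sample size calculation' plans 40 patients, adds nothing for loss and gives no dropout rate.

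**The concern.** The randomised contrast is active against sham stimulation during the first ten sessions, and T2 is the assessment closest to it. After T2 come 15 sessions alone at home and a visit one month later, so loss is most likely in the period after the most informative score has been collected.

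A classical group-by-visit ANOVA cannot use a partial row. A patient seen at T1 and T2 but not at T4 is removed, T2 score included, if the within factor spans all visits. If visits are analysed in pairs, the patient stays in T1 v T2 but adds nothing to the T3 and T4 comparisons, although T2 predicts what the later scores would have been. If patients with small T2 gains leave more often from one arm, those who remain no longer represent the randomised groups, and the tDCS effect is mis-estimated in a trial of 20 per arm.

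Training gain is exposed in the same way. If the later of its two points is the end of training, an early stopper has no value, although an N level was recorded at every completed session.

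**Working it through.** **1. The plan's own figure.** Inputs from 'Sample size calculation': effect size 0.73, alpha 0.05, power 0.80, stated N about 48. A two-sample t-test (noncentral t, 1:1) gives 24 per arm, N = 48, if one-sided, and 31 per arm, N = 62, if two-sided. The stated figure therefore reproduces as one-sided. It matters here only because neither 48 nor the planned 40 includes an allowance for loss.

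**2. Does the method need complete rows?** A standard repeated-measures ANOVA routine was run on 10 subjects by 4 visits (40 cells) with one cell missing. It refused the data as unbalanced. The subject must be deleted or the value imputed.

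**3. How many rows are lost?** No rate is documented, so assume each of T2, T3 and T4 is missed independently with probability p. The share missing at least one visit is 1 - (1 - p)^3.

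| p | Share incomplete |
|---|---|
| 0.05 | 1 - 0.95^3 = 14% |
| 0.07 | 1 - 0.93^3 = 20% |
| 0.10 | 1 - 0.90^3 = 27% |

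At p = 0.05 about 34 of 40 patients are complete over four visits, against 38 usable for T1 v T2. At p = 0.10 the figures are 29 and 36.

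**4. What does restriction to completers do to the estimate?** Simulation assumptions: 20 per arm; gains from T1 at T2, T3 and T4 with SD 1 and correlation 0.7; true effect 0.73 at each visit; loss after T2, more likely among patients with low T2 gain.

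| Patients lost (active v sham) | Completers, T2 | Completers, T4 |
|---|---|---|
| Equal in both arms | about 0.73 | about 0.73 |
| 3 v 1 | 0.84 | about 0.8 |
| 4 v 0 | 0.97 | 0.90 |
| 8 v 0 | 1.17 | 1.04 |

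Relative to 0.73, the T2 overstatement is 0.84/0.73 = 1.15, 0.97/0.73 = 1.33 and 1.17/0.73 = 1.60. In the two one-arm scenarios the likelihood estimate, which keeps all observed T2 scores, stays at 0.73 to 0.74.

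With equal loss the cost is precision at T2: standard error 0.323 v 0.314 at 10% lost (ratio 1.03) and 0.337 v 0.313 at 20% lost (ratio 1.08).

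**5. Equal numbers are not enough.** A second simulation used visit correlation 0.6 and about 20% lost in each arm, with loss in the active arm confined to below-median T2 gainers and random loss under sham. The completers' T1-T2 difference was +0.19 SD with no true effect, and 0.92 with a true 0.73. What matters is whether the reasons for leaving differ between arms.

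**6. Two-visit reading.** If only T1 and T2 enter the T2 analysis, the T2 column in step 4 does not apply, because the leavers' T2 scores are used. The T4 column still does.

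**The case against.** The strongest reply is that the article never states a four-visit ANOVA. A reader might infer that the plan cannot use anyone who misses a visit and that dropouts lose all their data. The text does not support that. The word 'including' leaves the list of methods open, the factors are only group and unspecified test variables, and no deletion rule appears. The outcome definitions include two-point contrasts, and a T1-T2 ANOVA keeps a patient who leaves later. The two points for training gain are not fixed either. The medication footnote ends participation; it does not say collected data are discarded. All of this stands, and the point is conditional for that reason.

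It is also fair that a missing-data rule or analysis set may sit in a document not shown, so its absence is not a finding. What remains concerns the method that is named. An open list does not put a mixed model in the plan, even though the listed software can fit one. The two-visit reading rescues only T2, and the usual non-parametric repeated-measures tests need complete rows too.

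Three further cautions hold:
- The Discussion describes reducing dropout; it does not forecast a rate.
- Loss from one arm only is a worst case. After T2 neither arm is stimulated and patients are blinded. Patients troubled by the current would mostly leave before T2, and those have no post-T1 test score for any model to use.
- At 0.73, two-sided, power falls from 61% with 20 per arm to 52% with 16. That is the cost of dropout, not what a mixed model recovers.

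**Conclusion.** The point holds in conditional form. Classical ANOVA across T1-T4 limits every contrast to patients with all visits. Classical ANOVA on pairs of visits still limits the T3 and T4 comparisons to completers and leaves their T2 scores unused. Either way a better method is available for the same data.

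The size rests on assumed loss. It runs from about no bias and a 3-8% larger T2 standard error (equal loss, same reasons), through about 0.84 at T2 for a true 0.73 (3 v 1 lost), to 0.97-1.17 at T2 in a worst case that should not be read as expected. The T2 figures apply to the four-visit form only. The change is worth making because the trial is small, has no reserve for loss and can adopt the alternative at almost no cost. Confidence is medium, because the intended form of the ANOVA is not stated.

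**What to change.** In 'Data collection, management, analysis, and monitoring':

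- **T1-T4 outcomes.** Replace the ANOVA with a linear mixed model fitted by REML. Responses: T2, T3 and T4. Terms: group, visit, group x visit and T1 score. Use an unstructured covariance over the three visits and small-sample (Kenward-Roger) degrees of freedom. Include every randomised patient with any post-T1 value, in the allocated arm, and read the T2, T3 and T4 group contrasts from this one model.
- **Session-level N level.** Use a mixed model with a parsimonious structure, for example a random intercept and slope over session, so that early stoppers contribute the sessions they completed. An unstructured covariance is not feasible here: 25 sessions imply 25 x 26 / 2 = 325 parameters from 40 patients.
- **Sensitivity and reporting.** Keep the completer ANOVA as a sensitivity analysis, and report missing visits with reasons by arm.

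Cost: wording only, with no new data or patients; R, already listed, fits both models. The models assume data are missing at random, which is weaker than what the completer analysis needs. The visit model does not recover patients with no post-T1 test score.
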